#### Biochemical measures

Participants will be required to fast at least 10 h before the study visit and return to the center between 6 and 10 am. They will be instructed to stop smoking and abstain from caffeine and alcohol 10 h before the study visit to ensure that all fasting blood samples are collected before taking medication in the morning. Biochemical tests, such as hematuria, will be completed at each center, and stool and blood samples of each participant will be collected and sent to professional institutions for the subsequent intestinal flora and metabolomics testing.

#### Participant diary

Each participant will be provided a participant diary and instructed to record blood glucose, blood pressure, weight, abdominal circumference, medication, diet, exercise, and adverse reactions, such as hypoglycemia. We will check and record the participant’s diary during each follow-up and return visit.

### Sample size calculation

This is a controlled trial aims at exploring the remission effect of canagliflozin on T2DM. The experimental group is the canagliflozin group, and the control group is the metformin group. The main observation index is the remission rate. We referred to relevant studies and set the remission rate for metformin as 20.9%, similarly the estimated remission rate of canagliflozin was also 20.9%. For non-inferiority design, the cut-off value was 2%, α = 0.025, and power = 0.80. The sample size calculated by PASS 15 software was 73 cases in each group, and at least 92 participants should be enrolled in each group at baseline, for a total of 184 participants.

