**Method:**

To this end, we performed a multicenter, parallel-group, randomized, controlled, and open-label trial. A total of 184 participants with a ≤ 3-year course of T2DM will be enrolled and randomly assigned to the canagliflozin or metformin treatment group in a ratio of 1:1. Participants in each group will maintain their medication for 3 months after achieving the target blood glucose level and then stop it. These participants will be followed up for one year to determine remission rates in both groups.

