### Data analysis

All statistical analyses will be performed by full-time statisticians using R Studio (Version 1.2.5001, R Studio Inc., Boston, MA, USA). The normality test will be used to determine whether the data are normally distributed. Continuous variables with a normal distribution will be reported as the mean ± SD, and ordinal and non-normally distributed variables will be reported as the median and interquartile range. Independent samples t-tests or Mann-Whitney U-tests will be used for comparisons, as appropriate. Categorical variables will be reported as counts and proportions, and the Pearson χ^2^ test or Fisher’s exact test will be used for comparisons, as appropriate.

The primary outcomes (remission rate 3 months after drug withdrawal and after 1 year of follow-up) will be compared between groups using Pearson’s χ^2^ test or Fisher’s exact test. Logistic regression will be used to adjust for potential confounders. Variables with P < 0.05 in the univariate comparisons, and known confounders that could impact the efficacy, will be included in the multivariable logistic regression models.

Subgroup analyses will be conducted of the primary outcomes stratified by age group (young, 18 ~ 35 years; middle-aged, 36 ~ 59 years; older, 60 ~ 65 years); duration of disease (<1 year, 1 ~ 2 years, 2 ~ 3 years); BMI (18.5 ~ 27.9 kg/m^2^, 28 ~ 40 kg/m^2^); and sex, using the same methods of analysis.

For the secondary outcomes, continuous data will be analyzed using the linear mixed effects model, which will use the random intercept model to explain the internal correlation of participants. Discontinuous data will be analyzed similar, but the generalized linear model appropriate to the distribution assumptions and link functions will be used. The analysis of all secondary outcome indicators also corrected for potential confounders (including variables with P < 0.05 in the univariate comparisons and known confounders that could have an impact on the efficacy). The safety indicators will be analyzed using the same methods used to analyze the main outcome indicators.

Missing values will be filled using multiple imputation methods, and sensitivity analyses will be performed.

Two-tailed P-values will be used, and P-values < 0.05 will be regarded as statistically significant. Point estimates will be reported with 95% confidence intervals.

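### The stated 73 per group does not give 80% power at the stated 2% non-inferiority cut-off: those inputs need about 6,488 per group, and 73 gives about 5% power if the true rates are equal

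*Protocol article*

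**What the plan says.** All inputs and the result stand together in the protocol article, Sample size calculation. The authors "set the remission rate for metformin as 20.9"%, and "the estimated remission rate of canagliflozin was also 20.9"%, so the assumed true difference is zero. The design is given as non-inferiority: "For non-inferiority design, the cut-off value was 2"%. The error rates are "α = 0.025, and power = 0.80". The result is reported as follows: "The sample size calculated by PASS 15 software was 73 cases in each group". Enrolment is then set higher, with a minimum of 92 per arm and 184 overall. No other margin appears anywhere in the article.

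Two other places bear on the point. The Discussion paragraph of the abstract and the Study objectives ask whether canagliflozin is superior to metformin. The Data analysis section plans Pearson chi-square or Fisher's exact tests of the remission rates and says "Two-tailed P-values will be used, and P-values < 0.05 will be regarded as statistically significant".

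**The concern.** A 2-point margin on a remission rate near 21% is very strict and normally needs thousands of patients per group. A result of 73 cannot be right for that margin at 80% power.

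This paragraph is the only justification given for the 184 participants cited in the abstract, the Study design section and the Randomisation and interventions section. A reader would take the trial to be well powered to rule out a loss of more than 2 percentage points. If the stated margin is the true one, the trial has almost no chance of doing so under its own assumption of equal rates. If a much wider margin was used, the article misreports it, and the wider margin protects very little of the metformin rate.

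**Working it through.** **Inputs** (Sample size calculation unless noted)
- Remission rate p = 0.209 in both groups, so the true difference is 0.
- Margin m = 0.02, read as an absolute difference in remission rates.
- Alpha = 0.025, sidedness not stated. It is taken as one-sided, which matches the two-tailed 0.05 in Data analysis. So z = 1.960.
- Power 0.80, so z = 0.842.
- Allocation 1:1 (abstract, Method: "randomly assigned to the canagliflozin or metformin treatment group in a ratio of 1:1").

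**Step 1: try to reproduce 73 from the stated inputs**

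n per group = 2p(1−p)(1.960 + 0.842)² / m²

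- 2 × 0.209 × 0.791 = 0.3306, and the squared sum of the z-values (unrounded) is 7.849.
- n = 0.3306 × 7.849 / 0.0004 = 6,488 per group, or 12,976 in total before dropout.
- 6,488 / 73 is about 89.

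The stated figure is not reproduced.

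**Step 2: does another convention rescue it?**

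| Variant, 2% as the margin | n per group |
|---|---|
| One-sided alpha 0.05 | 5,111 |
| Pooled or null variance | about 6,255 to 6,323 |
| One-sided alpha 0.025, unpooled | 6,488 |
| With continuity correction | about 6,588 |
| One-sided alpha 0.0125 | 7,857 |
| 2% as a relative margin | about 148,500 |

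None is near 73.

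**Step 3: power of the stated size at a 2-point margin, equal true rates**

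Power = Φ(m/SE − 1.960), with SE = √(0.3306/n)

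- n = 73: SE = 0.0673; 0.02/0.0673 − 1.960 = −1.663; power 4.8% (exact enumeration of the Wald test: 4.9%).
- n = 92: SE = 0.0599; 0.02/0.0599 − 1.960 = −1.626; power 5.2% (exact: 5.5%).

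**Step 4: precision**

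The 95% half-width is 1.960 × SE: 13.2 points at n = 73 and 11.8 points at n = 92.

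**Step 5: which margin does give 73?**

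- Solving for m at n = 73: m = 2.802 × 0.0673 = 0.1885.
- Taking m = 0.209 − 0.02 = 0.189: n = 0.3306 × 7.849 / 0.189² = 72.65, which rounds up to 73. Power at 73 is then 80.2%.
- A margin of 20 points (a slip of 2% for 20%) gives 65, or about 75 with continuity correction, not 73.
- Share of the control rate given up at 18.9 points: 0.189 / 0.209 = 90%.

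**Step 6: dropout step**

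73 / 0.80 = 91.25, which rounds up to 92. This step is sound if 20% dropout was intended.

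**The case against.** The arithmetic is not in dispute, and the inconsistency does not come from missing text or from detail left to another document. The objections concern how far the consequences reach.

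**The text says cut-off, not margin.** The exact match at 18.9 points makes a mislabelled input plausible: 2% as the lowest acceptable canagliflozin rate. This stands as a likely explanation, but the article does not say so. It does not rescue the wording, because 2% is presented as the cut-off of a non-inferiority design.

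**A reader might infer that, with a margin near 19 points, a canagliflozin rate of about 2% would pass.** That is not so. A true rate of 2% lies on the null boundary and would pass only about as often as a type I error: 3.8% at n = 73 and 3.9% at n = 92 by exact Wald enumeration. With metformin observed at 20.9%, canagliflozin would need an observed rate of roughly 14% (n = 73) or 13% (n = 92). What remains is that the margin itself tolerates a loss of about 90% of the control rate.

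**A reader might also infer that the trial can never exclude a 2-point deficit.** That holds only near equal rates. The trial hopes canagliflozin is better. If the true rates were 40.9% and 20.9%, the chance that the lower limit lies above −2 points would be about 83 to 84% at n = 73 (SE 0.0747; Φ(0.22/0.0747 − 1.960)) and 91% at n = 92. The 5% figure must therefore be stated as conditional on equal rates, which is the article's own planning assumption.

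**No non-inferiority test is planned.** Data analysis specifies two-tailed difference tests and the objective is superiority. This stands: withdrawing the power claim is not enough, because the size then has no stated justification for the objective being tested.

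**Conclusion.** The sample size statement is wrong as written. Under equal true rates of 20.9%, 73 per group has about 5% power at a 2-point margin, not 80%, and 92 per group is no better. The required size is about 6,488 per group. The conclusion rests on reading the cut-off as an absolute difference and alpha as one-sided, but no variant tried with 2% as the margin gives fewer than 5,111.

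Either the size is about 89 times too small for the stated margin, or the margin is misstated by a factor of about nine (18.9 against 2 points). The documents do not show which. The exact match at 18.9 points favours the second without proving it.

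**What to change.** In Sample size calculation:
1. Delete the claim that 73 per group gives 80% power at a 2% margin.
2. State the margin actually entered in the software, the scale it is on, the sidedness of alpha, and the share of the metformin rate it preserves. If it was 18.9 points, say plainly that this preserves about 10%.
3. Keep 184 participants and state what they deliver: a 95% confidence interval half-width of about 12 to 13 points on the remission-rate difference, and about 5% power to exclude a 2-point deficit if the true rates are equal.
4. Reconcile the non-inferiority sizing with the superiority objective (abstract; Study objectives) and the two-tailed tests (Data analysis), so that one hypothesis governs objective, size and analysis.
5. Do not describe the trial as powered for non-inferiority at 2 points.

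**Cost.** The restatement is a change of wording and needs no extra patients. The price is a much less favourable power statement. Whether 184 is enough for the hypothesis finally chosen is a separate question that step 4 will raise. By the article's own dates (publication in October 2023, recruitment from December 2023), the correction could have been made before enrolment began.

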### Data collection

All participants’ information will be collected and sorted by the full-time personnel in each center. After sorting, they will be checked by another staff member. After confirmation, the information will be uploaded to the Metabolic Management Center for timely storage to ensure the continuity and accuracy of participants’ inspection data. A confidentiality agreement shall be signed with the Metabolic Management Center, and each center shall appoint a network docking contact person responsible for data security assurance, storage, and export. The export of data shall be approved by the main researchers.

### Data analysis

All statistical analyses will be performed by full-time statisticians using R Studio (Version 1.2.5001, R Studio Inc., Boston, MA, USA). The normality test will be used to determine whether the data are normally distributed. Continuous variables with a normal distribution will be reported as the mean ± SD, and ordinal and non-normally distributed variables will be reported as the median and interquartile range. Independent samples t-tests or Mann-Whitney U-tests will be used for comparisons, as appropriate. Categorical variables will be reported as counts and proportions, and the Pearson χ^2^ test or Fisher’s exact test will be used for comparisons, as appropriate.

The primary outcomes (remission rate 3 months after drug withdrawal and after 1 year of follow-up) will be compared between groups using Pearson’s χ^2^ test or Fisher’s exact test. Logistic regression will be used to adjust for potential confounders. Variables with P < 0.05 in the univariate comparisons, and known confounders that could impact the efficacy, will be included in the multivariable logistic regression models.

Subgroup analyses will be conducted of the primary outcomes stratified by age group (young, 18 ~ 35 years; middle-aged, 36 ~ 59 years; older, 60 ~ 65 years); duration of disease (<1 year, 1 ~ 2 years, 2 ~ 3 years); BMI (18.5 ~ 27.9 kg/m^2^, 28 ~ 40 kg/m^2^); and sex, using the same methods of analysis.

For the secondary outcomes, continuous data will be analyzed using the linear mixed effects model, which will use the random intercept model to explain the internal correlation of participants. Discontinuous data will be analyzed similar, but the generalized linear model appropriate to the distribution assumptions and link functions will be used. The analysis of all secondary outcome indicators also corrected for potential confounders (including variables with P < 0.05 in the univariate comparisons and known confounders that could have an impact on the efficacy). The safety indicators will be analyzed using the same methods used to analyze the main outcome indicators.

Missing values will be filled using multiple imputation methods, and sensitivity analyses will be performed.

Two-tailed P-values will be used, and P-values < 0.05 will be regarded as statistically significant. Point estimates will be reported with 95% confidence intervals.

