### Study objectives

The primary objectives are to assess the effects of canagliflozin and metformin on diabetes remission and determine whether canagliflozin is superior to metformin. The secondary objective is to explore the possible underlying mechanisms by which the two medications elicit T2DM remission.

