### Outcomes

#### Primary outcome

Remission rates.

This is the percentage of participants in each group who meet the remission criteria during follow-up: HbA1c < 6.5% maintained for > 3 months after the treatment discontinuation [27].

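### Two primary time points are each tested at 0.05 and neither is named as the decider; if either may carry the claim, the false-positive rate is about 7 to 9%, not 5%

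*Protocol article*

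**What the plan says.** Three sections of the protocol article describe the primary endpoint differently.

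- **Primary outcome.** The heading is singular and the entry is "Remission rates". The definition reads "This is the percentage of participants in each group who meet the remission criteria during follow-up: HbA1c < 6.5% maintained for > 3 months" once treatment has stopped. It names no visit at which remission is judged.
- **Sample size calculation.** "The main observation index is the remission rate". One rate, 20.9%, is used for both groups, with no time attached.
- **Data analysis.** "The primary outcomes (remission rate 3 months after drug withdrawal and after 1 year of follow-up) will be compared between groups". Each of these comparisons is a chi-square or exact test. The threshold is general: "Two-tailed P-values will be used, and P-values < 0.05 will be regarded as statistically significant".

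The trial is meant to give one answer. Study objectives says it will "determine whether canagliflozin is superior to metformin". The Method part of the Abstract says that the year of follow-up serves to determine remission rates, but it does not say that the value at 1 year decides.

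**The concern.** With two primary tests, each at the full 0.05, and one superiority question, the text allows the claim to rest on whichever test succeeds. The two can disagree. Under Randomisation and interventions, a participant whose hyperglycemia recurs during follow-up counts as not in remission. Someone in remission at 3 months who relapses at 9 months is then a success on one primary outcome and a failure on the other.

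An early difference that has faded by 1 year could therefore be presented as the trial's result. The trial is open-label, so a decider chosen once results are emerging would carry little weight.

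**Working it through.** **The plan's own figures.** The plan states a per-test threshold of 0.05 and no trial-wide error rate, so there is no family-wise figure to reproduce. The stated 73 evaluable per group does not follow from its inputs: 2 × 0.209 × 0.791 × (1.960 + 0.842)² / 0.02² gives about 6,488 per group. That is a separate problem. Here 73 and 92 serve only as group sizes.

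**Inputs from the article.** Two tests, each at two-sided 0.05; 73 evaluable and 92 enrolled per group; 1:1 allocation; a remission rate of 20.9%.

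**Inputs assumed.** There is no true difference between groups. The 1-year remitters are a subset of the 3-month remitters, which the recurrence rule makes plausible but the article does not state. The article does not say which time 20.9% describes, so both placements are tried: 20.9% at 1 year with 25 to 50% at 3 months, and 20.9% at 3 months falling to 15% or 10% at 1 year.

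**Step 1: bounds.** With independent tests, 1 − 0.95² = 0.0975. With correlation 1, the two tests are one test and the rate is 0.05.

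**Step 2: correlation under nesting.** With p3 and p12 the rates at 3 months and 1 year, r = √[p12(1 − p3) / (p3(1 − p12))]. For p3 = 0.30 and p12 = 0.209: √[(0.209 × 0.70) / (0.30 × 0.791)] = √(0.1463 / 0.2373) = 0.785.

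**Step 3: chance of at least one significant result.** The normal approximation is P(|Z1| > 1.96 or |Z2| > 1.96) for a bivariate normal with correlation r. As a check, Pearson's chi-square was applied to every possible pair of nested remission counts, each weighted by its binomial probability. Simulation of 400,000 trials per scenario, in the scenarios simulated, agrees with this to about 0.1 percentage point.

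| 3 months / 1 year | r | Either test, normal approx. | Either test, 73 per group | Either test, 92 per group | False canagliflozin superiority, 73 / 92 |
|---|---|---|---|---|---|
| 25% / 20.9% | 0.89 | 7.1% | 7.1% | 7.1% | 3.5% / 3.6% |
| 30% / 20.9% | 0.79 | 7.9% | 7.9% | 7.9% | 4.0% / 4.0% |
| 40% / 20.9% | 0.63 | 8.6% | 8.8% | 8.5% | 4.4% / 4.3% |
| 50% / 20.9% | 0.51 | 9.0% | 9.6% | 8.7% | 4.8% / 4.3% |
| 20.9% / 15% | 0.82 | 7.7% | 7.7% | 7.6% | 3.8% / 3.8% |
| 20.9% / 10% | 0.65 | 8.6% | 8.7% | 8.6% | 4.3% / 4.3% |

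Part of the 9.6% comes from the coarseness of counts: with 73 per group and a rate of 50%, the 3-month chi-square test alone rejects in 5.7% of trials. Elsewhere in the table each single test lies between 4.6% and 5.2%.

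**Step 4: direction.** The either-test columns count differences favouring either drug. The last column counts only those favouring canagliflozin, for which a single two-sided test at 0.05 has a nominal rate of 2.5%. The relative inflation is the same.

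**The case against.** The strongest reply is that handling of multiplicity is often left to a statistical analysis plan or full protocol, and neither is shown. The plural entry under Primary outcome could also mean that Data analysis merely says when one outcome is read. The first part stands to this extent: a missing alpha split alone would be no finding. But the article goes further. It names two primary outcomes and one unadjusted threshold, which does not match one outcome and one planning rate elsewhere. A later document would have to correct this text, not only add to it.

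Three stronger readings are tempting and are not supported:

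- **That 7 to 9% is the chance of wrongly declaring canagliflozin superior.** It counts both directions; the figure for that claim is about half as large.
- **That the plan lets either time point suffice.** It does not say so. Requiring both to be significant would cause no inflation. The defect is that neither rule is given.
- **That the article makes 1 year the decider.** The Abstract gives only the purpose of follow-up, and the criterion of more than 3 months in the Primary outcome section does not point to 1 year.

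It is also fair to say that the 3-month rate, the nesting and the time point of 20.9% are assumptions. The size of the inflation depends on them, but the inconsistency between sections does not.

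**Conclusion.** The point holds. The article does not fix consistently which remission rate answers the primary question, and it sets two primary tests at full alpha.

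If either test suffices, the chance of at least one false significant result is about 7 to 9%, reaching 9.6% in the least favourable scenario with 73 per group, instead of 5%. A false claim of canagliflozin superiority has a chance of about 3.5 to 4.8% instead of 2.5%. Both results are conditional on the nesting and rates assumed above. Without those assumptions, only the two-sided range of 5% to 9.75% can be given, for correlations from 1 to 0.

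The α = 0.025 under Sample size calculation is no remedy: it belongs to a single non-inferiority comparison and is not described as a split between two outcomes. The inflation is moderate, and the matter should be settled before outcomes are compared.

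**What to change.** Before any outcome comparison, name one time point as the single primary outcome and state the same one under Primary outcome, Sample size calculation and Data analysis. Remission at 1 year is a reasonable suggestion because participants are followed for a year to determine remission rates, but the sponsor should confirm the choice.

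Test the other time point in fixed sequence, at two-sided 0.05, only if the primary test is significant. Otherwise report it descriptively with its 95% confidence interval. The chance of a false significant result in the pair is then held at the nominal 5% of the first test when neither time point truly differs.

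The wording change is short and by itself adds no participants. The sponsor must, however, check that the 20.9% planning rate refers to the chosen time point; if it does not, the planning rate has to be revisited. The downside is that an isolated difference at the non-deciding time point can no longer support the superiority claim.

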### Randomisation and interventions

A total of 184 participants will be randomly allocated to receive either canagliflozin or metformin treatment (1:1). The randomization operation will be generated by an independent statistician, who will ensure the balance of participants according to age, sex, HbA1c and BMI and course of their disease when grouping, and a code list will be directly allocated to the main investigators of every center. The intervention content of the two groups is as follows.

Canagliflozin treatment group: For oral treatment, the participants will receive canagliflozin tablets (Janssen-Cilag S.p.A., Ltd., National Drug Approval: H20170375) once daily, 100–300 mg per time, with a minimum dose of 100 mg per day and maximum dose of 300 mg per day.Metformin treatment group: For oral treatment, the participants will receive metformin hydrochloride tablets (Sino-American Shanghai Squibb Pharmaceutical Co., Ltd., National Drug Approval: H20023370 (0.5 g × 20 tablets)/Sino-American Shanghai Squibb Pharmaceutical Co., Ltd., National Drug Approval: H20023371 (0.85 g × 10 tablets × 2 plates)), 1–3 times a day, 500–2000 mg per time, with a minimum dose of 500 mg per day and maximum dose of 2550 mg per day.

Regarding weekly titration for oral drug metering, the titration targets are fasting blood glucose (FBG) (3.9–5.6 mmol/L) and blood glucose at 2 h after each of the three meals (5.0–7.0 mmol/L). After meeting the above criteria, the participants will continue the medication for 3 months and then stop.

Routine diabetes health education will be provided to all participants during the treatment period. Routine diet control and appropriate exercises will be planned. Follow-up will be conducted monthly for the first 3 months after the end of treatment and every 3 months thereafter for 1 year (Table 1; Fig. 2). Participants with FBG > 7.0 mmol/L and postprandial blood glucose (PBG) > 10 mmol/L during the follow-up period are defined as having hyperglycemia recurrence, which will be treated according to the Chinese guidelines for the diagnosis and treatment of T2DM and is defined as not remitted.

**Table 1 Tab1:** Participant visit schedule

**Research Stage**	**Screening**	**Baseline**	**Intervention Period**				**Follow-up Period**		

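### Allocation is balanced on five factors, yet the primary test uses none of them and the adjusted models pick covariates by univariate P < 0.05, not limited to baseline

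*Protocol article*

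**What the plan says.** Under Randomisation and interventions, the list is produced by an independent statistician, "who will ensure the balance of participants according to age, sex, HbA1c and BMI and course of their disease when grouping". The method of balancing is not named.

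Under Data analysis, the primary outcomes "will be compared between groups using Pearson’s χ^2^ test or Fisher’s exact test". Neither test uses the five factors. The next sentence adds a second analysis: "Logistic regression will be used to adjust for potential confounders". Its content is set by a rule: those below the 0.05 threshold "in the univariate comparisons, and known confounders that could impact the efficacy, will be included in the multivariable logistic regression models". The section does not say whether the univariate comparisons are between arms or between remitters and non-remitters, which confounders count as known, or that only baseline variables may enter.

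The rule is carried over to the rest of the efficacy analysis: "The analysis of all secondary outcome indicators also corrected for potential confounders", again with P < 0.05 and known confounders as the entry conditions.

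**The concern.** Three features of the stated method work against the trial.

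First, factors important enough to balance on are left out of the test. If they predict remission, balancing makes the true spread of the remission difference smaller than the chi-square test assumes, so the test is conservative and loses power. The article itself treats some of them as prognostic. The Background says that a shorter course raises the chance of remission and cites a cohort in which short course and low HbA1c went with remission. The planned subgroups are age, duration, BMI and sex.

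Second, a P < 0.05 screen is a poor way to choose covariates in a randomised trial. If the screen compares arms, it picks up chance imbalance and will tend to miss the very factors that allocation has balanced. If it compares remitters with non-remitters, the outcome chooses the model. Either way the covariate set is unknown until the data are in, in an open-label trial.

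Third, nothing confines the rule to baseline. The Background names weight loss, insulin resistance and β-cell function as routes of the drug effect, and weight and HOMA indices are secondary outcomes. As worded, the rule does not shut out their on-treatment values.

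**Working it through.** **The plan's own figure.** Under Sample size calculation, remission is 20.9% in both arms and "For non-inferiority design, the cut-off value was 2%, α = 0.025, and power = 0.80", giving 73 per group. The usual formula with these inputs gives n = 2 × 0.209 × 0.791 × (1.960 + 0.842)² / 0.02² ≈ 6,488 per group, so 73 is not reproduced. That is a separate matter. Here 73 per group is used only as the number of evaluable patients: 2 × 73 = 146.

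**Events available.** 0.209 × 146 = 30.5 and 0.209 × 184 = 38.5, so about 31 to 38 remissions. With arm plus five covariates (6 parameters), 30.5 / 6 = 5.1 and 38.5 / 6 = 6.4 events per parameter.

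**Simulation.** 146 patients, 20.9% control remission, 2,000 trials per scenario, two-sided 0.05. Assumptions not in the documents:
- allocation by minimisation on the five factors (biased coin, probability 0.8);
- SD of the prognostic linear predictor 0, 0.7, 1.0 or 1.5 on the log-odds scale;
- conditional log odds ratio 1.0 for power.

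Three analyses were compared: chi-square (crude), logistic regression with all five factors (fixed), and logistic regression with those of the five that reach P < 0.05 against remission (selected). Best of three means that any one of them rejects.

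| SD | Power: crude / fixed / selected | Type I error: crude / fixed / selected | Type I error: best of three |
|---|---|---|---|
| 0 | 0.787 / 0.793 / 0.784 | 0.050 / 0.051 / 0.047 | 0.058 |
| 0.7 | 0.707 / 0.742 / 0.726 | 0.052 / 0.060 / 0.056 | 0.069 |
| 1.0 | 0.637 / 0.708 / 0.688 | 0.033 / 0.046 / 0.041 | 0.056 |
| 1.5 | 0.513 / 0.625 / 0.615 | 0.029 / 0.043 / 0.041 | 0.051 |

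Monte Carlo standard error is √(0.05 × 0.95 / 2000) ≈ 0.005 for type I error and √(0.7 × 0.3 / 2000) ≈ 0.010 for power. All analyses in a row use the same simulated trials.

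**Fixed minus crude, power.** 0.6 points at SD 0, then 3.5, 7.1 and 11.2 points.

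**Fixed minus selected, power.** 0.9, 1.6, 2.0 and 1.0 points.

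**Why the crude test is conservative.** Its standard error at 20.9% is √(2 × 0.209 × 0.791 / 73) ≈ 0.067. The simulated SD of the crude risk difference under the null is 0.064 at SD 1.0 and 0.061 at SD 1.5.

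**Precision.** Under the null, the SD of the risk difference, crude to standardised from the fixed model, goes 0.069 to 0.069, 0.068 to 0.067, 0.064 to 0.063 and 0.061 to 0.058. With a treatment effect at SD 1.5 it goes 0.069 to 0.065, a fall of 0.004 / 0.069 ≈ 6%. The median SE of the log odds ratio moves the other way: 0.413 to 0.424, 0.411 to 0.443, 0.411 to 0.459 and 0.411 to 0.497.

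**The case against.** The adjusted analysis is already planned, so a fair test of the covariate rule is fixed against selected, and that is worth only 1 to 2 points. This stands. The larger gain belongs to making an adjusted result primary in place of the crude test.

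A reader might infer that P-values after this selection are invalid. The simulations do not support that: screening among the five baseline factors gave type I error of 0.041 to 0.056. Wider pools of candidates were not tested.

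A reader might also infer two competing primary results. The natural reading of Data analysis is that the crude test is primary and the logistic model supportive. What remains is that the order is not stated outright, and with an unnamed covariate set several analyses can be reached. The best-of-three column shows the cost of choosing after the fact, but the plan does not say that anyone will choose, and only the 0.069 at SD 0.7 lies clearly above 0.05.

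Nor does the plan propose adjusting for on-treatment weight or HOMA. It speaks of confounders, which suggests baseline variables. The supportable point is only that the text does not say so.

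The known confounders may well include the five factors, and a full protocol or SAP may list them. That could complete the list, but it would not remove a P-value rule that the article states for the primary adjusted model and for all secondary outcomes.

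Finally, the power figures rest on assumed prognostic strength, effect and allocation method. This stands, and is why a range is given.

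**Conclusion.** The point holds as a stated choice of method that can be improved almost for free. It is not a fault that invalidates the trial. If the balancing factors are prognostic to the degree assumed (SD 0.7 to 1.5), the crude primary test gives up about 4 to 11 points of power, and at SD 1.0 and 1.5 it runs below its nominal level (0.033 and 0.029). If they are not prognostic, nothing material is lost or gained.

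It would be too broad to say that adjustment is more precise. That is true of power and, modestly (0 to about 6%), of a standardised risk difference. It is untrue of the log odds ratio, whose standard error rises while its meaning becomes conditional on the covariates. The case against P-value selection rests less on power than on leaving the model open until the data are seen and on not excluding post-randomisation variables.

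**What to change.** In Data analysis:

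- Delete selection by P < 0.05 for the primary and all secondary outcomes, and replace the unnamed known confounders with a list.
- Name one primary analysis: logistic regression of remission on arm plus baseline age, sex, HbA1c, BMI and disease course, with continuous factors as linear terms. Report the standardised remission-rate difference with 95% CI. Keep the chi-square or Fisher test as supportive.
- Allow baseline covariates only.
- For continuous secondary outcomes, use the same five factors plus the outcome's own baseline value.
- Do not require a random intercept for centre in the primary model. About 5 to 6 events per parameter leave little room for more terms.

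The cost is a few sentences and slightly more programming. No new data are needed, since all five factors must be known at allocation, and the sample size is not changed by this point.
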